##### Patient Optimism Scale (POS)

2.2.5.6

The POS was developed based on a cancer-related patient optimism scale and adapted for burn survivors (41). The authors defined optimism as the ‘patient’s belief that he or she had made appropriate choices regarding his or her treatment and the patient’s hopefulness about treatment outcomes’. The scale is part of a measure that assesses patient fortitude, trust in nurses (health care providers) and authentic self-representation. Participants are asked to answer each question using a six-point scale ranging from 1 (never) to 6 (always). Scores are then transformed into a 0–100 range, with higher numbers reflecting higher levels of optimism (41). The Cronbach’s alpha coefficient for the scale was 0.75, and the item–scale correlations ranged from 0.44 to 0.65 (41).

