**Methods and analysis:**

This cohort study will follow 600 participants (*n* = 600; *n* = 500 burn survivors; *n* = 100 caregivers) with three measurement points at 6- to 12-month intervals. The primary outcomes are knowledge, attitudes and practices regarding burn injuries. The secondary outcomes are meaning in life; gratitude, resentment and appreciation; hope; optimism; temporal satisfaction with life; coping strategies; social interaction anxiety; self-stigma and resilience, measured using the Meaning in Life Questionnaire, the Gratitude, Resentment and Appreciation Scale, the Adult Workers Hope Scale, the Patient Optimism Scale, the Temporal Satisfaction with Life Scale, the COPE Inventory, the Social Interaction Anxiety Scale, the Self-Stigma Scale and the Brief Resiliency Scale, respectively. The participants are grouped as follows: the exposure group (i.e., burn survivors [*n* = 200] and caregivers [*n* = 100] exposed to campaign messages), the non-exposure group (i.e., burn survivors [*n* = 250] not exposed to campaign messages) and the Photovoice group (i.e., burn survivors [*n* = 50] who participate in Photovoice and are exposed to the campaign messages). This design evaluates the impact of the health communication campaign and determines whether Photovoice has any additional effects on the primary and secondary outcomes.

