### Research design

2.1

This study is a cohort study with three measurement points conducted at 6- to 12-month intervals (*n* = 600). The impact of the health communication campaign will be evaluated by measuring indicators of knowledge, attitudes and practices related to burn first aid, as well as psychological variables and health information-seeking variables, among the following groups: the exposure group (i.e., burn survivors [*n* = 200] and caregivers [*n* = 100] exposed to campaign messages), the non-exposure group (i.e., burn survivors [*n* = 250] not exposed to campaign messages) and the Photovoice group (i.e., burn survivors [*n* = 50] who participate in Photovoice and are exposed to the campaign messages). Figure 1 presents the campaign process and the planned activities in different phases.

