### Phase 0: baseline assessment

2.2

The research team will recruit participants (*n* = 600) from seven project sites across Pakistan for a baseline assessment measuring existing indicators of knowledge, attitudes and practices on burn prevention, psychological variables, health information-seeking variables and demographics (see Table 1 for the full list of variables).

**Table 1 tab1:** Outcome measures collected at the data collection points throughout the study.

Outcome measures	Baseline (t0)	Time 1 (t1)	Time 2 (t2)
KAP ^1,2^	X	X	X
SSS-S^1^	X	X	X
GRAT^1^	X	X	X
MLQ^1^	X	X	X
WHS^1^	X	X	X
CPOS^1^	X	X	X
TSWLS^1^	X	X	X
COPE^1^	X	X	X
SLAS^1^	X	X	X
BRS^1^	X	X	X
Photo Reflection^1,2,3,4*^		X	X
Campaign effectiveness^1,2,3,4^			X

Survivors^1^; family members ^2^; health care professionals^3^; key informants^4^; the photo reflection workshops are for burn survivors only except for the workshops conducted at the end of the public exhibitions^*^; t0, baseline; t1, end of photo reflection workshop; t2, end of closed exhibitions; t3, end of closed exhibition; t4, end of the final public project exhibition; KAP, Knowledge Attitude and Practice Scale; MLQ, Meaning in Life Questionnaire; GRAT, Gratitude and Resentment Scale; WHS, Adult Workers Hope Scale; CPOS, Patient Optimism Scale; TSWLS, Temporal Satisfaction with Life Scale; COPE, COPE Inventory; SIAS, Social Interaction Anxiety Scale; SSS, Self-Stigma Scale; BRS, Brief Resiliency Scale.

Ethical approval was obtained from the Pakistan National Bioethics (Approval ID: NBC-985) and Manchester University Research Ethics Committees (Approval ID: 2023–18,027-31199).

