## Data analysis plan

4

To compare changes in self-reported outcomes within groups across two time points (see Table 1) in the sample (*N* = 600), we will implement linear mixed-effects models implemented in R (R version 3.6.1) (51) using the lme4 package and in SAS 9.4. This method considers correlations within participants, allowing them to be modelled appropriately. It also estimates within-subject variability, in addition to estimating model parameters. The method can handle and model missing outcome data under the assumption that the data are missing at random. The mixed model uses a longitudinal data structure that includes both fixed and random effects, and baseline measurement is usually included as a covariate. Time will be included in the model as an interacting categorical variable to observe any time-varying trends. Cohen’s *d* for the effect of Photovoice will be calculated as the difference between baseline-corrected estimated means divided by the pooled standard deviation. A two-sided *p* < 0.05 indicates statistical significance. In addition, demographic variables, such as age, education, gender, marital status, geographic location (i.e., rural vs. urban residence) and household situation (i.e., living with a single and/or an extended family) will be included in the linear mixed models to test for potential moderating and mediating effects on behavioural intention related to burn prevention and first-aid practices. A stepwise selection of the variables will be conducted to determine which variables to keep in the model. As we add the variables, we will immediately eliminate those that do not reduce the Akaike information criterion (AIC) by using the *stepAIC* R function from the library *MASS*. If two or more independent variables in a model are found to be strongly correlated, a variance inflation estimate of less than 5 will be used to determine whether collinearity is present. If the relationship is found to be non-linear, attempts will be made to model the outcome data via the use of splines or polynomials in the *nlme* package in R. The normality of residuals will be assessed graphically using histograms and Q-Q plots. Detailed statistical analyses following Good Clinical Practice: Consolidated Guidelines ICH E9 (52) and Medical Research Council guidelines for developing complex interventions (53) will be described in the statistical analysis plan, which will be finalised before the data lock stage.

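### The only optimism measure concerns treatment but is given to survivors at any stage, so within-group change can reflect treatment course as well as the campaign

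*Protocol article*

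**What the plan says.** The abstract lists optimism among the secondary outcomes and gives it a single instrument: "the Adult Workers Hope Scale, the Patient Optimism Scale, the Temporal Satisfaction with Life Scale". Section 2.2.5.6 describes that instrument as "developed based on a cancer-related patient optimism scale and adapted for burn survivors" and defines what it measures as the patient's "belief that he or she had made appropriate choices regarding his or her treatment", together with hope for how treatment turns out. The adapted items are not reproduced.

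Table 1 marks the scale for survivors at t0, t1 and t2. It uses a different abbreviation there, but the footnote identifies the instrument ("CPOS, Patient Optimism Scale"). Section 2.1 sets "three measurement points conducted at 6- to 12-month intervals", and the sample size paragraph that closes section 2.2.5 places the last follow-up at 24 months.

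The survivor criteria in section 2.2.4.1 accept a burn from the last three months or any earlier burn. They set no upper limit on time since injury and do not require the survivor to be under treatment.

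The comparison group in section 2.1 is "burn survivors [*n* = 250] not exposed to campaign messages". The data analysis plan (section 4) opens with this purpose: "To compare changes in self-reported outcomes within groups across two time points". It names linear mixed-effects models and a set of demographic variables, and says that the baseline measurement is usually a covariate.

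**The concern.** The scale asks about treatment, while the sample is not defined by treatment. Recruitment through burn-centre waiting rooms and consultations (section 2.2.3), combined with snowball sampling (section 2.2.1), can bring together people in active care and people whose care ended long ago. Over visits 6 to 12 months apart, a recently burned survivor may well pass from acute care to rehabilitation to no treatment. The score can move along that path whatever the campaign does.

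Two conclusions are at stake. A rise or fall in POS within the exposed or Photovoice group could be credited to the campaign when part of it is the ordinary course of treatment. And a score about treatment could be reported under the broader label of optimism that the abstract gives it.

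**Working it through.** There is no figure in the protocol to reproduce, so the check sets the sections side by side and then shows the size of the problem on assumed values.

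**What the sections establish together**

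1. Construct: treatment choices and treatment outcomes (section 2.2.5.6). No other optimism instrument is listed (abstract; Table 1).
2. Who answers: survivors with a burn of any age, in treatment or not (section 2.2.4.1).
3. When: t0, t1 and t2 (Table 1), 6 to 12 months apart (section 2.1).
4. First-named contrast: change within groups (section 4). In that contrast, drift caused by the course of treatment and any effect of the campaign cannot be separated. Adjusting for the baseline score corrects for where a person started, not for later movement out of treatment.
5. Between groups: 250 unexposed survivors complete the same scale. Drift that they share with the exposed survivors cancels. Nothing described makes treatment stage alike across groups. Sampling is purposive and snowball, no randomisation is described, and Photovoice members must also be willing to do creative work and free to attend workshops (section 2.2.4.1), which may relate to stage of recovery. The covariates named in section 4 are demographic.

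**Size, on assumed values**

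Let p be the share of a group that finishes treatment between two visits, and d the mean shift in POS among those people, in SD units and in either direction. Assume that d is the same in each group and that others do not drift.

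- Within-group bias = p × d
- Between-group bias = d × (p exposed − p unexposed)

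The protocol gives neither p nor d. The illustration takes d from 0.2 to 0.5.

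| p exposed | p unexposed | Within exposed group | Between groups |
|---|---|---|---|
| 0.5 | 0.5 | 0.5 × 0.2 = 0.10 to 0.5 × 0.5 = 0.25 | 0 |
| 0.5 | 0.3 | 0.10 to 0.25 | 0.2 × 0.2 = 0.04 to 0.2 × 0.5 = 0.10 |
| 0.6 | 0.2 | 0.6 × 0.2 = 0.12 to 0.6 × 0.5 = 0.30 | 0.4 × 0.2 = 0.08 to 0.4 × 0.5 = 0.20 |

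The within-group contrast carries the whole drift. The between-group contrast carries only the imbalance, and none if the shares are equal.

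**The case against.** The strongest reply is that the protocol never says the scale concerns current treatment. The first half of the definition looks back at choices already made, and a survivor can rate those after treatment has ended. Outcomes of treatment may also stay open for a long time, since the introduction describes lasting consequences of burns and complications such as contractures. The scale has been adapted for burn survivors, and without the items nobody can say that they presuppose ongoing care. All of this stands. A reader might infer that the scale is meaningless for survivors out of treatment, and the document does not support that. What remains is narrower: the forward-looking half may have a less clear referent once treatment is over, and the protocol does not say how the scale applies then.

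A second reply is that the design has an unexposed group and that the abstract rests the evaluation of the campaign on the groups. That also stands. It limits the firm part of the point to within-group change and makes between-group confounding conditional on imbalance.

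A third reply is that the covariates in section 4 are given as examples, that section 2.2.5 leaves room for further demographic items, and that details go to a separate analysis plan. The absence of treatment status from this article is therefore not in itself an error. But an analysis plan cannot adjust for something that was not collected, so the decision belongs at the data collection stage.

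**Conclusion.** The point holds in a limited form. The only optimism measure is specific to treatment, it is repeated in survivors at unrestricted stages after injury, and the contrast named first cannot tell the course of treatment from the effect of the campaign. On the assumed values with half a group finishing treatment, that contrast is off by 0.10 to 0.25 SD.

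A reader might go further and infer that the campaign result for optimism is confounded in any case. The documents do not show this. Against the unexposed group the bias is zero when equal shares finish treatment, and 0.04 to 0.20 SD under the two imbalanced scenarios. Whether such imbalance will occur is unknown. It is possible because allocation is not described as random and neither variable is named for adjustment.

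The consequence is confined to one of nine secondary instruments. The primary knowledge, attitudes and practices outcomes and the sample size are untouched. The differing abbreviation in Table 1 is clerical.

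**What to change.** 1. Record time since burn at t0, and add one yes/no item at every visit on whether the survivor is currently receiving burn treatment or rehabilitation.
2. Keep all survivors in the POS model. Adjust for, or stratify by, the baseline values of these two variables, allow their effect to differ by visit, and keep them in whatever the stepwise selection does.
3. Base the campaign effect on the between-group contrast, and present within-group change as descriptive.
4. Use restriction to survivors still in treatment only as a sensitivity analysis, because it selects on status after baseline. It would also leave little in the Photovoice group: 50 × 0.8 = 40 remain after the planned 20% dropout, and if half of those were still in treatment (assumed), 20.
5. State how the scale is to be answered once treatment has ended, report the outcome as optimism about burn treatment, and make no claim about general optimism. Use one abbreviation throughout.

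The cost is one or two short items, a few lines of analysis wording and a narrower claim for one secondary outcome. Baseline adjustment will not remove differences in treatment course that arise only after t0. The visit-level item lets these be described.

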##### Temporal Satisfaction with Life Scale (TSWLS)

2.2.5.7

The TSWLS measures three temporal dimensions of life satisfaction: past, present and future (42). It consists of 15 items assessing individuals’ global life satisfaction, separated based on three temporal dimensions (i.e., past, present and future satisfaction). Respondents rate their agreement with each item on a seven-point Likert-type scale ranging from 15 (strongly disagree) to 75 (strongly agree). All 15 items are positively keyed. Four scores can be obtained for the analyses. First, summing all 15 items leads to a total score ranging 15 to 105. Second, summing the five items for each temporal dimension (past, present and future satisfaction) provides three subscale scores ranging from 5 to 35 (42).

##### COPE Inventory

2.2.5.8

The COPE Inventory is a measure of dispositional tendencies to adopt particular coping styles (43). The scale identifies the personality characteristics that might predispose individuals toward a particular way of coping with stress. The COPE Inventory is a 60-item measure comprising 15 subscales with four items each. The subscales are planning, active coping, suppression of competing activities, restraint, use of instrumental support, use of emotional support, positive reinterpretation and growth, acceptance, religious coping, focusing on and venting emotions, denial, behavioural disengagement, mental disengagement, substance use and humour. Individuals are asked to indicate the extent to which they use these coping strategies when encountering difficult or stressful events in their lives. The dispositional COPE Inventory coefficients ranging from 0.45 (mental disengagement) to 0.92 (turning to religion) in a large sample of 978 undergraduates (43).

##### Social Interaction Anxiety Scale (SIAS)

2.2.5.9

Social interaction anxiety refers to distress experienced when meeting and talking to people, specifically ‘fears of being inarticulate, boring, sounding stupid, not knowing what to say or how to respond within social interactions, and being ignored’ (44). We have included this measure of social anxiety because levels of social anxiety reflect the degree to which people are motivated to make impressions on others but doubt that they will make the impressions they desire (44). Respondents indicate the degree to which each statement is characteristic or true of them on a five-point Likert-type scale ranging from 0 (not at all) to 4 (extremely). The Cronbach’s alpha coefficients exceeded 0.88 for all five initial samples (44, 45). Inter-item reliability exceeded 0.85 (46).

##### Brief Resiliency Scale (BRS)

2.2.5.10

The BRS is a six-item self-report scale (47). Sample items include the following: ‘I tend to bounce back quickly after hard times’; ‘I have a hard time making it through stressful events’; ‘It does not take me long to recover from a stressful event’; and ‘It is hard for me to snap back when something bad happens’. The response options for all items are ordered on a five-point Likert-type scale. The scale demonstrated appropriate internal consistency, with Cronbach’s alphas ranging from 0.80–0.91 across four samples in the study (47).

The sample size calculation for the study is based on a comparison of the baseline and follow-up measures of the primary outcome, knowledge of burn-related prevention, in this cohort study. Using a previous study as a reference (22), we determined that a sample size of 478 is required to achieve a 70% improvement in knowledge of burn-related prevention, assuming a 63% rate of poor knowledge at baseline, a 5% significance level and 91.5% power at the 24-month follow-up (last follow-up). A total of 600 participants will be required, with a 20% dropout rate taken into account.

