##### Knowledge Attitudes And Practice (KAP) Scale

2.2.5.1

The KAP includes a range of structured interviewer-administered questions to obtain a better understanding of knowledge, attitudes and practices regarding burn injuries (22, 34). The knowledge- and attitude-based questions include 10 items, scored on a four-point Likert scale ranging from strongly disagree to strongly agree. Higher scores represent better knowledge of and favourable attitudes toward burn injuries and first aid. The practice of burn first aid includes 12 questions with various response formats, such response categories such as ‘true/false’ and ‘yes/no’. A sample item for the knowledge-based questionnaire is, “Burns lead to permanent injuries?’ A sample item for the attitude-based questionnaire is, ‘Do you think that applying dough, oil, mud, toothpaste, etc. on the wound delays the healing process?’ A sample item for the practice of burn first aid is, ‘In case of a burn injury, have you ever applied cold water?’ The internal consistency, measured using Cronbach’s alpha, was 0.887 for the knowledge-based questionnaire, 0.716 for the attitude-based questions and 0.758 for the practical questions (22).

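### The sample-size statement mis-describes its effect: 478 at 91.5% power fits a one-sample test of 63% versus 70%, neither a 70% improvement nor the before-and-after comparison described

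*Protocol article*

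**What the plan says.** The sample-size paragraph stands at the end of section 2.2.5.10 (Brief Resiliency Scale) of the Protocol article. It makes four statements.

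- **Design.** The calculation is "based on a comparison of the baseline and follow-up measures of the primary outcome, knowledge of burn-related prevention". That is one cohort measured twice.
- **Baseline.** It proceeds "assuming a 63% rate of poor knowledge at baseline", taken from a cited earlier study.
- **Effect and size.** It concludes that "a sample size of 478 is required to achieve a 70% improvement in knowledge of burn-related prevention, assuming a 63% rate of poor knowledge".
- **Error rates.** It assumes "a 5% significance level and 91.5% power at the 24-month follow-up (last follow-up").

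The total is then raised to 600 for 20% dropout. Section 4 (Data analysis plan) sets two-sided testing at 0.05. The paragraph does not say whether the 70% is a relative change, an absolute change or a target rate, and it gives no within-person correlation.

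**The concern.** The two percentages are on opposite scales: 63% is a rate of poor knowledge, while 70% is described as an improvement. A 70% improvement from that baseline is a very large effect, and in a paired comparison it should need far fewer than 478 people. If instead 63% is set directly against 70%, the effect is only 7 points and, with 63% labelled as poor knowledge, the change would be a worsening.

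This paragraph is the only justification given for 600 participants. As it stands, a reader cannot tell what change the cohort is sized to detect, or whether the 91.5% applies to the before-and-after comparison that the paragraph describes.

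**Working it through.** **Inputs from the article:** baseline 63% poor (so 37% not poor); 70%; n = 478; power 91.5%; 5% significance, two-sided (section 4); dropout 20%. **Assumed, because not given:** the within-person correlation ρ, shown over a range.

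Constants: z for two-sided 5% = 1.960; z for 91.5% power = 1.372; (1.960 + 1.372)² = 11.10.

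**1. Reproducing the plan's figure.** One-sample test of 0.63 versus 0.70, variance taken at 0.70:

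- n = 11.10 × 0.70 × 0.30 / 0.07² = 476.
- Power at 478: 0.07 / √(0.21/478) = 3.340; 3.340 − 1.960 = 1.380; power = 91.6%. With the noncentral t it is 91.5%.
- Other versions of the same test at n = 478 do not match: score 89.9%, arcsine 90.1%, exact binomial 88.6%, one-sided versions 93.6% to 95.5%.
- Dropout: 478 / 0.8 = 597.5, rounded to 600. This step is sound.

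**2. A 70% improvement, read literally.** Paired (McNemar) comparison with rates p0 and p1 and difference d:

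- discordant share ψ = p0(1−p1) + p1(1−p0) − 2ρ√[p0(1−p0)p1(1−p1)]
- n = (1.960√ψ + 1.372√(ψ − d²))² / d²

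Example, good knowledge 37% to 62.9% (37% × 1.7), ρ = 0: ψ = 0.37 × 0.371 + 0.629 × 0.63 = 0.5335; d = 0.259; n = (1.960 × 0.7304 + 1.372 × 0.6830)² / 0.0671 = 84.

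| Reading | Pairs, ρ = 0 | Pairs, ρ = 0.3 | Pairs at maximum discordance |
|---|---|---|---|
| Poor falls by 70% relative: 63% to 18.9% | 29 | 22 | 43 |
| Good rises by 70% relative: 37% to 62.9% | 84 | 61 | 161 |
| Good reaches 70%: 37% to 70% | 52 | 38 | 91 |

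Only the second reading can pass 100, and only with negative correlation (107 at ρ = −0.3). With 478 pairs, power is about 100% in all three at the correlations tried (−0.3 to 0.5 where feasible). A rise of 70 percentage points is impossible, since 37 + 70 = 107.

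**3. 63% versus 70% as the paired comparison described.** d = 0.07. At ρ = 0, ψ = 0.63 × 0.30 + 0.70 × 0.37 = 0.448, and power with 478 pairs comes from (0.07√478 − 1.960√0.448) / √(0.448 − 0.0049) = 0.328, which gives 63%.

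| Assumed ρ | ψ | Power with 478 pairs | Pairs for 91.5% |
|---|---|---|---|
| 0 | 0.448 | 63% | 1,011 |
| 0.3 | 0.315 | 78% | 710 |
| 0.5 | 0.227 | 90% | 510 |

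Using 480 completers (600 × 0.8) instead of 478 does not change these rounded powers.

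**The case against.** The strongest reply is that the number is not wrong. The two percentages in the sentence give 478 at 91.5% by a standard formula, and the dropout step follows. This stands. A reader might infer that 478 matches no effect at all, or that 91.5% can be reached only with an unstated within-person correlation a little above 0.5. Neither inference is supported, because the one-sample test reaches the figure with no correlation. The fault is in the description, not in the arithmetic.

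A second reply is that the phrase about improvement is loose, and that the cited earlier study, which is not at hand, may define its knowledge rates in a way that explains it. That is possible. It would explain where the numbers came from, but the sentence would still name a different effect, on a different scale, from the one that yields 478.

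A third reply is that an article may leave the name of the test and the correlation to a fuller document. Omission alone would indeed be no finding. Here the stated effect, design, size and power do not fit one another.

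A reader might also object that the calculation uses a binary rate, while section 2.2.5.1 describes a score ("Higher scores represent better knowledge of and favourable attitudes toward burn injuries and first aid") with no cut-off and section 4 says "we will implement linear mixed-effects models implemented in R". That is not an error. The cut-off is detail that a condensed article may leave out, and sizing on a dichotomy while analysing a score is common practice.

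**Conclusion.** The point holds as a mis-described effect attached to a power figure from a different comparison. The 478 and 91.5% fit a one-sample test of 63% versus 70%. That this test was used is an inference from the numerical match. Such a test differs from the text in three ways: the difference is 7 points rather than a 70% improvement, it mixes a poor-knowledge rate with an improvement target, and it ignores the sampling error of the measured baseline.

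The gap is large in both directions. Under the three literal readings, 22 to 84 pairs suffice at correlations of 0 and 0.3, higher feasible correlations need no more than these, and 161 is the ceiling over all possible discordance. Under a paired 63% versus 70% comparison, power is about 63% to 90% for correlations from 0 to 0.5. All paired figures rest on the normal approximation and on assumed correlations.

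A reader might infer that the study is underpowered, or that the stated figures can be reconciled in no way. The documents support neither. The true power depends on the intended target and on the correlation, which are not given, and the figures do agree with one another under the one-sample 63% versus 70% reading.

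**What to change.** Keep 600 and rewrite the paragraph:

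1. Replace the 70% improvement with the actual baseline and follow-up rates on one scale, either both poor or both good knowledge.
2. Name the test used for the calculation.
3. State the assumed within-person correlation, ideally with a range.
4. Restate the power that about 480 completers give for the paired baseline-to-follow-up comparison.

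The dropout step can stay. The cost is one paragraph and no extra participants. The downside is that the stated power, or the effect that the cohort can detect, may look less favourable than it does now.

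### The target and the 91.5% power are stated for a proportion with poor knowledge, but the analysis named is a linear mixed model of a graded score

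*Protocol article*

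**What the plan says.** Three parts of the protocol article bear on this.

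- **Sample size paragraph, end of section 2.2.5.10.** The calculation rests on a "comparison of the baseline and follow-up measures of the primary outcome, knowledge of burn-related prevention". The number of participants is that "required to achieve a 70% improvement in knowledge of burn-related prevention", "assuming a 63% rate of poor knowledge at baseline", with a 5% significance level and 91.5% power at a 24-month last follow-up. The result is 478, raised to 600 for 20% dropout.
- **Section 2.2.5.1, KAP scale.** "The knowledge- and attitude-based questions include 10 items, scored on a four-point Likert scale ranging from strongly disagree to strongly agree". Higher scores mean better knowledge. No score is named below which knowledge counts as poor.
- **Section 4, data analysis plan.** For changes in the self-reported outcomes of Table 1, whose first row is the KAP, "we will implement linear mixed-effects models implemented in R". Residuals are checked for normality, the Photovoice effect is a difference in estimated means divided by a pooled SD, and "A two-sided *p* < 0.05 indicates statistical significance". Details are left to a statistical analysis plan to be finalised before data lock.

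**The concern.** A rate of poor knowledge is a proportion: each person has to be classed as poor or not poor. A linear mixed model of the KAP score estimates means. The power statement and the named analysis therefore concern different quantities, and the article gives no rule linking them.

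Two things are at stake. First, a reader will take 91.5% as the power of the planned test, and it is not. Second, the planned test cannot tell whether the stated improvement was reached. A mean can rise because people who already answer well move from agreement to strong agreement, while the share with poor knowledge stays where it was.

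**Working it through.** **Inputs from the article:** 63% poor at baseline (so 37% not poor); 70% improvement; 5% significance, two-sided according to section 4; 91.5% power; 478 evaluable; 20% dropout; 600 in total. Normal quantiles: z(0.975) = 1.960, z(0.915) = 1.372.

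**1. The plan's own figure.** Dropout: 478 / 0.8 = 597.5, so 598, which agrees with 600.

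The 478 itself depends on what a 70% improvement means. It cannot be 70 percentage points: 63 − 70 is negative, and 37 + 70 = 107 exceeds 100. The other readings were tried with three standard formulas:

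- one sample: n = [1.960·√(p0(1−p0)) + 1.372·√(p1(1−p1))]² / (p1−p0)²
- two samples, per group: n = [1.960·√(2p̄(1−p̄)) + 1.372·√(p0(1−p0)+p1(1−p1))]² / (p1−p0)²
- McNemar, pairs: n = [1.960·√ψ + 1.372·√(ψ−d²)]² / d², where ψ is the discordant proportion, d the change, and the within-person correlation is assumed

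| Reading | One sample | Two samples, per group | McNemar pairs (assumed correlation) |
|---|---|---|---|
| Poor falls by 70% of itself: 63% to 0.3 × 63 = 18.9% | 12 | 26 | 28 to 22 (0 to 0.3) |
| 70% not poor at follow-up: 63% to 30% poor | 23 | 49 | 52 to 29 (0 to 0.5) |
| Not poor rises by 70% of itself: 37% to 1.7 × 37 = 62.9% | 39 | 81 | 84 to 45 (0 to 0.5) |
| 63% against 70% of the same quantity | 507 | 1008 | 1011 to 409 (0 to 0.6) |

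Example, second row, one sample: [1.960 × 0.4828 + 1.372 × 0.4583]² / 0.33² = 1.575² / 0.1089 = 22.8, so 23.

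In the first three rows, 478 gives power above 99.9%. The fourth row comes nearest: a one-sample test with 478 has 89.9% power, and McNemar would give 478 at a correlation of about 0.53. But that reading conflicts with the text, where 63% is the rate of poor knowledge and 70% is an improvement. The figure is not reproduced. What matters for this point is that every reading treats the endpoint as a proportion.

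**2. The two statements side by side.**

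| | Sample size paragraph | Sections 2.2.5.1 and 4 |
|---|---|---|
| Variable | poor or not poor | graded score, higher is better |
| Summary | proportion | mean |
| Needed for power | two rates and, for pairs, a correlation | SD, mean difference, correlation |
| Given | baseline rate and an undefined improvement | none of the three |

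**3. What 478 would mean on the score scale.** With complete pairs and equal variance at both times, the detectable change in SD units is (1.960 + 1.372)·√(2(1−ρ)) / √478. The correlation ρ is assumed:

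- ρ = 0.3: 0.18 SD
- ρ = 0.5: 0.15 SD
- ρ = 0.7: 0.12 SD

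A link to the stated target needs further assumptions that the article does not make. If scores were normal with the same SD at both times, moving the poor share from 63% to p would need a mean shift of z(0.63) − z(p) SD: 1.21 for p = 18.9%, 0.86 for p = 30%, and 0.18 for a 7-point fall to 56%. The first two are far above what 478 pairs detect. The last equals the detectable change at ρ = 0.3 and exceeds it at 0.5 and 0.7. This is an illustration, not a power calculation for the study.

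**The case against.** The strongest reply is that this is a condensed article. Section 4 names linear mixed models for the self-reported outcomes as a class, does not say that no other model will be used, and leaves detail to an analysis plan that is not shown. That plan could hold both a cut-off and a responder analysis. The cut-off may also exist in the reference study, which the article cites both for the KAP scale and for the sample size. Finally, sizing on a dichotomised outcome and analysing the underlying score usually costs no power.

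Much of this stands, and it rules out several stronger readings that a reader might infer:

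- **That the proportion is never analysed.** The article shows only that it names no such analysis.
- **That the missing cut-off is itself an error.** A scoring rule can properly sit in the analysis plan.
- **That the sample size paragraph defines success as a responder endpoint.** It states a planning assumption. The abstract gives the primary outcomes simply as knowledge, attitudes and practices.
- **That the study is underpowered.** Nothing in the article shows it.
- **That the result would swing by a known amount with the cut-off.** The article gives no mean or SD, and does not make clear whether the 10 items are for knowledge alone, so even the score range is uncertain.

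The reply does not remove the mismatch. The article itself fixes both the scale of the power statement and the model, and they do not agree.

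**Conclusion.** The point holds as a mismatch between two things the article states. The target and the 91.5% power belong to a proportion with poor knowledge; the named analysis is of a graded score. The 91.5% is therefore not the power of the named analysis, and a mean difference from that analysis cannot show whether the target was reached.

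The effect on power cannot be given a size, because the inputs for the score scale are absent. The conclusion rests only on reading the 63% as a proportion of people and the linear mixed model as a model of the KAP score; the residual checks and the standardised mean difference in section 4 support the second. It does not depend on whether 478 is arithmetically right. It concerns a primary outcome and is cheap to correct.

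**What to change.** Bring the two statements into line by either route.

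- **(a) Keep the score.** Leave the linear mixed model as the main analysis and restate the sample size and power on the score scale, giving an SD, a target mean difference and a within-person correlation with their sources.
- **(b) Keep the proportion for the power statement.** Before data lock, fix the cut-off for poor knowledge in section 2.2.5.1, using that of the reference study if it applies to this scale. Add to section 4 a pre-specified binary repeated-measures analysis of the proportion with poor knowledge at the last follow-up, for example a logistic mixed model reported as a risk difference with 95% CI. Name it as the analysis to which the power statement refers, alongside the score model.

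In both routes:

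- State whether the 70% improvement is absolute, relative or a follow-up rate. Under (a), say how it relates to the target mean difference.
- Reconcile the 24-month follow-up with the schedule. Table 1 has columns only to t2, and its footnote labels t2 as the end of the closed exhibitions. Section 2.1 has three measurement points at 6- to 12-month intervals, so the last falls 12 to 24 months after baseline and reaches 24 only if both intervals are at their longest.

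The cost is a revised paragraph under (a), or one scoring rule and one further model on data already collected under (b). The downside is small: under (a) the stated power may change, and under (b) the binary analysis is less sensitive than the score, which is why the score model stays beside it.
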